#### Secondary outcome

The secondary outcomes are derived from the CHMP Guidelines on clinical investigations of migraine [9] and include:Number of headache days/monthNumber of days with attack aborting medication per monthTime to MO or MOHSeverity of headachesDisability due to headache (Migraine-specific disability assessment (MIDAS)-Score)Psychiatric comorbidity (Depression, Anxiety, and Stress Scale (DASS)-Score)Frequency of serious adverse events (SAEs)For patients who have reached the primary endpoint during the study: number of headache days/month and number of days with attack aborting therapy per month in the last study month

### Participant timeline {13}

Table 1 gives an overview of the trial time schedule.

**Table 1 Tab1:** Table of scheduled activities

Tasks	Screening	Baseline	Visit 1^**a**^	Visit 2^**a**^	Visit 3 End of trial/early withdrawal
	28 days prior to randomization	Day 0	Day 112 ± 7 days	Day 224 ± 7 days	Day 336 ± 7 days
**Informed consent**^**b**^	X				
**Inclusion/exclusion criteria**	X	X			
**Assessment of compliance with the app**		X	X	X	X
**Current headache treatment**	X	X	X	X	X
**Concomitant medication/supplement check**	X	X	X	X	X
**Randomization**		X			
**Medical history**	X		X	X	X
**Clinical data/additional lifestyle factors**		X			
**MIDAS**		X			X
**DASS**		X			X
**Assessment of headache days**	Continuously via app				
**Assessment of headache episodes**	Continuously via app				
**Confirmation of app-based outcome event assessment**			X	X	X
**SAE assessment**		X	X	X	X

^a^Study visit 1 and visit 2 can exceptionally be conducted via a phone call if local regulations (e.g., due to a pandemic such as SARS-CoV-2) prohibit a personal study visit

^b^Informed consent has to be obtained prior to any study-related procedures at the screening visit

*DASS* Depression, Anxiety and Stress Scale, *MIDAS* Migraine-specific disability assessment

#### Screening

Before screening, written informed consent will be obtained prior to enrollment and all trial-related procedures. Date of informed consent, subject age, gender, and reason for ineligibility (if subject is not eligible) will be documented. After screening for assessable inclusion and exclusion criteria, the patient will be trained for all relevant aspects of function and data entry with the app. Current headache treatment and medical history will be documented. In the upcoming screening phase of 28 days, the patient will use the app for data entry only. No message will be generated within the screening phase. Within the screening phase, the compliance of the patient to use the app on a regular basis will be calculated by the app. The level of compliance is one inclusion criterion necessary for randomization at baseline visit and has to be ≥ 80%.

#### Baseline

After patients have completed a screening phase of 28 days with a sufficient level of compliance (≥80% days with entered headache days and days with acute medication) and the inclusion and exclusion criteria are still fulfilled, they will be allocated to one condition (migraine patients or post-MO(H) patients) and subsequently randomized into one of the two study groups (control group or treatment group). After randomization, current headache therapy, concomitant medication/supplements, psychiatric comorbidity (via DASS), and disability due to migraine (via MIDAS) as well as additional lifestyle factors will be assessed and recorded in the eCRF.

#### Visit 1 and visit 2

The compliance with the app will be assessed. Furthermore, the current headache treatment, concomitant medication/supplements, and newly diagnosed concomitant diseases will be captured together with the documentation of possible outcomes or SAEs.

To minimize the potential risk of an infection with SARS-CoV-2, this may be conducted via a regular telephone call based on local regulations in effect at the time of the scheduled visit.

#### Visit 3

The compliance with the app will be assessed. Furthermore, the current headache treatment, concomitant medication/supplements, and newly diagnosed concomitant diseases will be captured together with the documentation of possible outcomes or SAEs. Psychiatric comorbidity (via DASS) and disability due to migraine (via MIDAS) will be assessed and recorded in the eCRF.

### *Sample size {14}*

The sample size calculation is based on the comparison of two independent proportions using a *z*-test at a significance level *α* = 0.05. Calculations were performed using PASS 13. Based on data from the literature [10–12], we estimate the transition rate from frequent EM/CM to MOH to be 10% per year, and the relapse rate after MO(H) treatment to be 40%. Plausible target occurrence rates for the treatment groups are 4% in the migraine category and 25% in the post-MO(H) category [10–12], which correspond to effect sizes (relative reduction rates) of 60% in the migraine category and 38% in the post-MO(H) category.

Aiming at a power of 1−*β*= 0.8, a sample size of N_mig_ = 2 × 283 = 566 patients for the migraine category is necessary for the ITT analysis to detect a difference in MOH occurrence proportion of 6 percentage points between patients receiving direct feedback and patients receiving unspecific messages. With the same values for significance and power as above, a sample size of N_MO(__H)_ = 2 × 152 = 304 patients for the post-MO(H) category is necessary to detect a proportion difference of 15 percentage points in MO(H) relapse.

We increased the sample size to N_mig_ = 624 and N_MO(H)_ = 336 in the studied categories to compensate for loss to follow-up; thus, a total *n* = 624 + 336 = 960 patients are to be recruited for the trial.

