### Outcomes {12}

#### Primary outcome

The primary outcome was defined due to its relevance to estimating MO prevalence and the associated costs [8].Proportion of patients developing MO or MOH for at least 3 consecutive months between baseline and end of study visits.

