#### Primary outcome

The null and alternative hypotheses are as follows for migraine patients/post-MO(H) patients:

H0 (mig): Direct specific feedback and unspecific messages compared to unspecific messages alone do not change the rate of migraine patients developing MO or MOH/relapsing after treatment of MO(H).H1 (mig): Direct feedback and unspecific messages compared to unspecific messages alone change the rate of migraine patients developing MO or MOH/relapsing after treatment of MO(H).

The primary outcome (proportion of patients with MO/MOH until end of follow-up) will be compared separately in each patient category (EM/CM patients and post-MO(H)-patients) between the treatment groups, using Pearson’s chi-square test or Fisher’s exact test, if expected frequencies are below five, aiming at demonstrating a difference to compare the null and alternative hypotheses. The null hypothesis in each group can be rejected if the two-sided *p*-value related to the appropriate test statistic is smaller than or equal to *α*=0.05. Since the hypotheses will be tested independently in each patient group, no correction factor for multiplicity needs to be applied to the significance level. In addition, the odds ratio effect of the treatment on MO(H) will be calculated in each patient category using conditional logistic regression models on the data, conditioning on matched recruitment strata, and taking into account further prognostic factors.

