### *Methods in analysis to handle protocol non-adherence and any statistical methods to handle missing data {20c}*

Missing values in the primary outcome will be categorized as “missing at random” (MAR) or “missing not at random” (MNAR) depending on the patient’s answer. MAR will be assumed in case of failure to contact the patient, if the patient stopped for a reason unrelated to health issues or if no answer is provided. MNAR will be assumed if patients are lost to follow-up due to (perceived) lack of efficacy, worsening condition or if missing data is due to technical problems of the app. The classification will be finalized on a case-by-case basis prior to database lock. Cases judged as MNAR will be counted as treatment failures and included in the ITT set. For all cases where MAR is likely, multiple imputation will be used (to be detailed in the statistical analysis plan (SAP)) Detailed specification of the ITT and PP populations and other robustness analyses will be also specified in the protocol and the SAP.

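### The 80% power stated for the migraine category is not supported for the analysis the protocol prescribes, chiefly because some lost patients are counted as treatment failures

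*Protocol article*

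**What the plan says.** All places are in the protocol article.

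- **Sample size {14}.** The calculation is done "using a *z*-test at a significance level *α* = 0.05" and "Aiming at a power of 1−*β*= 0.8". For migraine patients, "we estimate the transition rate from frequent EM/CM to MOH to be 10% per year"; the feedback-arm target is 4%, and the difference to be detected is 6 points in MOH occurrence. This gives 2 × 283 = 566. For post-MO(H) patients the plan takes "the relapse rate after MO(H) treatment to be 40" per cent, with no time unit, against 25% for MO(H) relapse. This gives 2 × 152 = 304. The totals are raised to 624 and 336 "in the studied categories to compensate for loss to follow-up".
- **Outcomes {12}, Primary outcome.** "Proportion of patients developing MO or MOH for at least 3 consecutive months". The outcome assessment text under {18a} defines MO and MOH separately.
- **Participant timeline {13}, Table 1.** The last visit is on day 336 ± 7.
- **Sequence generation {16a}.** Each randomized patient belongs to the ITT set.
- **Missing data {20c}.** Losses through perceived lack of efficacy, worsening or technical problems of the app are classed as MNAR. "Cases judged as MNAR will be counted as treatment failures and included in the ITT set". MAR cases are multiply imputed.
- **Statistical methods {20a}, Primary outcome.** Each category is tested separately: "The null hypothesis in each group can be rejected if the two-sided" p-value is at most 0.05.

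**The concern.** The sample-size section describes one analysis and the rest of the protocol prescribes another. In the migraine category there are three differences.

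1. **Loss.** Raising N by loss alone restores power only if lost patients drop out and the remaining rates stay at 10% and 4%. Under {20c} some of them stay in as events. A loss caused by an app fault has no evident link to whether feedback works, so it adds events to both arms, shrinks the difference and raises the variance. With a control risk of only 10%, a few such events matter.
2. **Endpoint.** The rate is for MOH; the test is on MO or MOH.
3. **Time.** The rate is annual; the schedule ends at day 336.

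Because each category is tested on its own, the migraine comparison depends on its own power. If that power is well below 80%, a null migraine result could be misread as evidence against feedback.

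**Working it through.** **Inputs.** Two-sided α 0.05, power 0.80, 1:1 allocation; rates 10% vs 4% and 40% vs 25%; planned N 566 and 304, recruited 624 and 336 ({14}, {16a}, {20a}).

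**1. The plan's own figures.** The pooled z-test without continuity correction is

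n per arm = [1.960·√(2p̄(1−p̄)) + 0.842·√(p₁(1−p₁)+p₂(1−p₂))]² / (p₁−p₂)², with p̄ the mean of the two rates.

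This gives 282.7, so 283, and 151.9, so 152. Power at those sizes is 80.04% and 80.03%. The arithmetic is correct for its inputs.

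**2. Implied loss.** 1 − 566/624 = 9.3% and 1 − 304/336 = 9.5%. The protocol gives no percentage.

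**3. Failure rule alone.** Let L be the loss and s the share of it counted as failure. The share s is not stated, so a range is shown. Assume equal loss in both arms and no information from MAR cases. With N recruited per arm (312 or 168):

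- analysed n = N·(1 − L(1−s))
- failure-counted fraction q = Ls / (1 − L(1−s))
- each arm's rate becomes q + (1−q)·p

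Migraine, s = 25%: n = 312 × (1 − 0.0697) = 290.2; q = 0.0232/0.9303 = 0.0250; rates 12.25% and 6.40%.

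| s | Migraine rates | Migraine power | Post-MO(H) rates | Post-MO(H) power |
|---|---|---|---|---|
| 10% | 10.9% vs 5.0% | 74.9% | 40.6% vs 25.8% | 79.2% |
| 25% | 12.3% vs 6.4% | 67.9% | 41.5% vs 26.9% | 77.9% |
| 50% | 14.4% vs 8.7% | 58.7% | 43.0% vs 28.8% | 76.0% |

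The optimistic bound treats MAR cases as carrying full information: n = 312 and q = Ls. Migraine power is then 78.9%, 71.9% and 61.7%. With no loss at all, 312 per arm at 10% vs 4% gives 83.7%.

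**4. Day 336 alone.** Under a constant hazard, p(336) = 1 − (1−p)^(336/365). The migraine rates become 9.24% and 3.69%. Power is 76.8% at 283 per arm, or 80.7% at 312 per arm with no loss. If 40% and 25% were also annual, which is an assumption, they become 37.5% and 23.3%: 77.3% at 152 per arm, or 81.3% at 168.

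**5. Wider endpoint alone, migraine, 283 per arm.** The control rate for MO or MOH is not given, so the values below are assumptions.

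| Control rate | Relative reduction kept at 60% | Difference kept at 6 points |
|---|---|---|
| 12% | 87.2% | 70.4% |
| 15% | 93.9% | 59.4% |
| 20% | 98.6% | 47.6% |

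**6. Effects together, migraine.** Day 336 with s = 50% and a 10% annual control rate gives 53.9%. With a 15% annual control rate and a 60% reduction, day 336 and s = 50% give 79.7%.

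**The case against.** A reader might infer that the 80% is not delivered and that power is overstated in both categories. The documents do not support that, for these reasons.

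- **Post-MO(H) was sized differently.** Its rate has no time unit and already refers to MO(H) relapse, so the annual-rate and endpoint mismatches are not shown there. The failure rule costs it about 2 to 4 points at s = 25% to 50%.
- **Day 336 may be the trial's own twelve months.** It equals twelve 28-day periods, the screening phase is also 28 days, and the text speaks of 12 months. Taken literally it costs about 3 points, and only once the loss allowance is used up.
- **The wider endpoint can help the sponsor.** If MOH is only part of MO or MOH, the control rate is higher. Section {14} also states its effect as a 60% relative reduction, and on that scale power rises.
- **The failure-counted share is unknown.** Section {20c} sends failed contact, non-health reasons and missing answers to imputation, and classifies case by case before database lock. Counting every loss as a failure would contradict that rule.
- **Equal arms is an assumption.** Inefficacy and worsening may be commoner without feedback. At s = 25%, day 336 and twice as many failure-counted losses in the control arm, migraine power is 84.5%.

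All of this stands, and it removes any firm statement that power is below 80%. It does not make the stated 80% valid. Section {14} names neither the tested endpoint nor the failure rule in the migraine calculation, and app-fault losses give no clear reason to expect a control-arm excess.

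**Conclusion.** The concern holds for the migraine category as lack of support for the stated 80%, not as proof of a shortfall. The failure rule is the substantive part: 74.9%, 67.9% or 58.7% power when 10%, 25% or 50% of a 9.3% loss counts as failure (78.9%, 71.9% or 61.7% if MAR cases carry full information). These figures assume equal loss in both arms and 10% vs 4% otherwise. The endpoint mismatch is real but its direction is undetermined: at a 15% control rate, power is 94% or 59% depending on which effect scale is held. The time mismatch is small. Post-MO(H) is little affected; there the open point is the missing time horizon for 40% and 25%. The defect lies in the inputs, not in the calculation.

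**What to change.** **Sample size {14}:**

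- Restate the migraine control and feedback rates for MO or MOH over 336 days.
- State the time horizon of the 40% and 25%.
- State the assumed loss and the share of it expected to count as failure, by arm if they are expected to differ.
- Restate power, or the detectable difference, at 624 and 336.

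**Missing data {20c}:** stop counting losses due to app technical problems as treatment failures and multiply impute them. Keep failure counting for lack of efficacy or worsening. This removes the failures least related to the intervention and recovers part of any lost power.

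**Cost:** a less certain or less favourable stated power, and a short change to the missing-data text. Enrolment stays as planned.

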### *Recruitment {15}*

All participating sites signed a declaration of commitment including a feasibility questionnaire listing an approximate number of patients in the last 12 months with the indication of interest, who fulfill the inclusion/exclusion criteria and could most likely be recruited. Based on these declarations, the target sample size of 960 patients in total will be more than reached.

## 
Assignment of interventions: allocation

### *Sequence generation {16a}*

In order to achieve comparable groups, patients in each category will be allocated by concealed central randomization. A 1:1 block randomization of variable block length with stratification by indication, site, age (≤ or > 30 years), and sex will be performed to achieve balanced factor distributions for these relevant predictors. The randomization will be conducted centrally by the Center for Clinical Trials Essen (Zentrum für klinische Studien Essen; ZKSE) using a Web-based randomization tool with an audit trail (ALEA) and each patient who is randomized will be part of the ITT analysis set.

### *Concealment mechanism {16b}*

Treating physicians will generate a randomization code, which is entered in the study dashboard provided by Curelator (N1-Headache dashboard). As only authorized people from ZKSE and Curelator have access to the randomization list, the treating physician is blinded during randomization.

### *Implementation {16c}*

Described under the sections “Sequence generation {16a}” and “Concealment mechanism {16b}.”

## 
Assignment of interventions: blinding

### *Who will be blinded {17a}*

Patients and treating physicians will be blinded during randomization. Patients will not be informed in which group they are nor are they going to be asked if they can assume in which group they are.

However, it is possible that patients will become aware in which group they are, based on the feedback they receive. Once they make an appointment with their site due to a feedback message, the physician will know in which group the patient was randomized into. Because the primary endpoint is derived from data entered in the app, the lack of physician blinding is unlikely to introduce bias.

### *Procedure for unblinding if needed {17b}*

No emergency unblinding is necessary in this trial. It is possible that patients will become aware in which group they are, based on the feedback they receive.

## 
Data collection and management

### *Plans for assessment and collection of outcomes {18a}*

A clinical data management system (CDMS) with an audit trail will be used for all data collected at participating study sites in accordance with the study protocol and the eCRF. All patient-reported data will be stored separately on independent servers and transferred to ZKSE via a monthly export routine.

#### Current headache treatment

Patients document their medication intake daily via the app including the exact name of the substance. In addition, during regular trial visits, all medication will be recorded electronically via eCRF. If patients connect their mobile device to the Internet, entered data will be directly transferred, saved, and stored on the respective servers. Otherwise, data is stored locally on the respective mobile device until a connection to the Internet is available.

#### Medical history

Medical history including the assessment of concomitant diseases which might interfere with the study will be recorded at screening visit to allow group allocation and evaluation of inclusion/exclusion criteria. Medication for migraine prophylaxis and concomitant intake of other relevant substances will be documented. During study visits 1–3, newly diagnosed concomitant diseases (since the last visit) will be captured.

#### Outcome assessment

Relevant clinical data and additional lifestyle factors include information about depression, anxiety disorder, chronic back pain, sport activities, smoking, and drinking behavior as well as shift work.

The primary outcome is MO or MOH defined according to International Classification of Headache Disorders (ICHD-3, 8.2) criteria of MO and MOH [13]. According to ICHD-3, MO is defined as regular overuse of acute or symptomatic headache medication (on ≥ 10 days/month with specific migraine medication or ≥15 days/month of simple analgesics) for more than 3 months and MOH is defined as headache occurring on 15 or more days/month in a patient with a pre-existing primary headache and developing as a consequence of MO. In this study, the primary endpoint is reached when the intake thresholds or headache days are exceeded for ≥ 3 months [8].

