### Trial design {8}

This trial will be conducted according to the professional code for physicians in Germany §15 and is designed as a randomized, controlled, parallel, allocation-blinded multicenter, prospective trial with two arms. The effects of providing feedback to migraine patients regarding their self-reported use of migraine medications will be monitored using the app “N1-Headache” on the development of MO or MOH over 12 months after randomization.

Patients with qualifying migraine or a history of MO(H) will be recruited in different ways: First, through their physician at a participating headache center or medical practice. Second, through an advertisement for this trial sent by Curelator to German-speaking users of the public available Curelator app, directing interested patients to a participating site. Third, through cooperation with the German Headache Society (DMKG) and the MigräneLiga e.V, a self-help organization who will provide information about the trial within the respective section on their homepage. In addition, some study sites might publish a pre-approved template on their homepage to inform about the trial.

Informed consent will be obtained in the participating center through the investigator and a screening for the inclusion and exclusion criteria will be carried out. Medical history will be assessed for the determination of headache type and current treatment as well as actual medication intake. To facilitate the documentation of medication, the attack aborting medication documented during the screening visit will be handed out to patients as a printout to be entered in the app.

After patients have completed a screening phase of 28 days with a sufficient level of compliance (≥80% days of recording headache and medication use) and if the inclusion and exclusion criteria are still fulfilled, they will be allocated to one condition (migraine patients or post-MO(H) patients) and subsequently randomized into one of the two study groups (control group or intervention group). The control group will receive unspecific messages providing information on general trigger factors or latest migraine research highlights. The intervention group will receive the same unspecific messages and also direct feedback on their medication use through warning messages when predefined limits of frequent medication use are reached or passed.

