### Intervention description {11a}

N1-Headache is a digital platform (consisting of the N1-Headache app and the N1-Headache dashboard) that allows individuals with a history of migraine to track their headache outcomes (e.g., frequency, severity, and duration of attacks), migraine-related disability, medication use, and their potential migraine risk factors. For the MOH-DE study, the commercially available N1 platform was modified (e.g., onboarding and daily questionnaire, app settings, feedback customization) to comply with necessary study-specific adjustments and requirements.

Daily tracking of headache days, medication, and headaches and migraine risk factors is done through a visual interface that uses Visual Migraine Language^TM^ (VML), a set of icons developed with headache specialists and designed to facilitate the data entry of migraine symptoms and up to 70 migraine attack-related risk factors selected from a presented list, plus any custom factors the individual wants to track. Significant associations are presented to the user as a set of maps designed to show the results of their personal risk factor analysis.

The app is self-explanatory with a help icon behind each question where a detailed description of the question or answers is provided. In addition, a manual with all important questions is linked within the app.

Unspecific messages providing information on general trigger factors for migraine attacks or the latest migraine research highlights will be sent once a month to both groups to increase the general engagement with the app.

The intervention will be applied by means of alerts about the risk of overuse of certain classes of medication commonly used to treat headache/migraine or other conditions but which may also cause medication overuse headache. N1-Headache calculates the current risk of MO based on all the medications taken by an individual to treat migraine attacks and sends alerts to the user. Thresholds have been defined in accordance with the current ICHD-3 guidelines and are the same for all patients in the intervention arm.

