A challenge of the study is to combine the need of reliable statistical analysis tools to test the proposed study hypothesis with the need to allow fast market implementation in case of positive study results. For the post-study statistical analysis, it is of high importance that the underlying mechanisms of how study data was generated and collected is stable and robust and protected from permanent changes. These requirements are per se contradictory to the usual development cycles of mobile applications, which aim to improve the product for consumers in repeating loops. The proposed study design serves the interests of both sides due to study length and update regulations. First, a 1-year observation per patient and a total study duration of 2 years make it likely that applications on mobile devices are still a state-of-the-art technology used by a high percentage of people. Second, a steady-state application (protected from “cosmetic” updates) ensures that patients included at a later time point in the study will experience the same environment as patients enrolled early in the trial. Therefore, collected data remains comparable.

A possible limitation might be that recruiting physicians will treat both randomized patient groups more intensely than in usual care. This could lead to equipoise for the two treatment arms.

An advantage of the presented study is that the proposed study objective is suitable to be transferred to potential future technologies and therefore is quite sustainable as the platform will be a tool to answer the study question, not the cause of the obtained results. As the study wants to test the impact on direct feedback, positive results can most likely be translated to other forms of feedback as well. In the future, this does not necessarily need to be limited to app-based systems.

The strength of the study is the high number of planned patients and the rigorous design which compares the app including the electronic diary with additional warning messages if predefined thresholds of acute medication use are reached. Reaching those thresholds will result in an advice to contact the physician who will start an intervention (for example change of prophylaxis) according to clinical guidelines. Therefore, the study is part of a real-word setting and not in a totally artificial setting.

### 
Trial status

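### The sentence that sets the primary endpoint requires the monthly limits to be exceeded, while the definition just before it counts a month that only reaches them

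*Protocol article*

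**What the plan says.** All references are to the Protocol article.

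- **Outcomes {12}, Primary outcome** gives the duration (at least three months in a row) but no monthly inequality. The monthly cut-off therefore comes from Outcome assessment.
- **Outcome assessment (under {18a})** says the outcome follows ICHD-3. The intake limits are "on ≥ 10 days/month with specific migraine medication or ≥15 days/month of simple analgesics", and MOH is "headache occurring on 15 or more days/month in a patient with a pre-existing primary headache". All three limits are inclusive. The next sentence gives the rule for this trial: "In this study, the primary endpoint is reached when the intake thresholds or headache days are exceeded for ≥ 3 months".
- **Exclusion criteria** treat current MO inclusively, from 10 intake days a month upwards. **Inclusion criteria** describe the earlier overuse of post-MO(H) patients inclusively too.
- **Trial design {8}** has the intervention arm receive "warning messages when predefined limits of frequent medication use are reached or passed". The **Discussion** speaks of "additional warning messages if predefined thresholds of acute medication use are reached". **Intervention description {11a}** adds: "Thresholds have been defined in accordance with the current ICHD-3 guidelines". No section gives a number for the alert limit.

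**The concern.** Two neighbouring sentences give different answers for a month at exactly the limit. Under the definition, 10 days of specific migraine medication is an overuse month. Under the endpoint sentence it is not. A patient with 10 such days in each of 12 months would meet the intake limit every month, and every month would count towards the MO exclusion at entry, yet the intake rule would never make that patient an event. A sequence of 12, 10, 12 days is a qualifying run under one reading and a broken run under the other.

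Monthly counts are small whole numbers, and current overusers are excluded at entry, so months at exactly the limit should not be rare. According to Who will be blinded {17a}, the primary endpoint is derived from data entered in the app. An algorithm must therefore use either > or ≥, and the published text supports both. At stake are the event rate, and so the power, of both confirmatory comparisons.

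**Working it through.** **1. The plan's own sample size.** Inputs from Sample size {14}: 10% against 4% (migraine), 40% against 25% (post-MO(H)), α = 0.05, power 0.80. The two-sided test is stated in the statistical section and the 1:1 allocation in Sequence generation {16a}. For the pooled z-test,

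n per arm = [1.960·√(2p̄(1−p̄)) + 0.842·√(p₁(1−p₁)+p₂(1−p₂))]² / (p₁−p₂)²

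- Migraine: p̄ = 0.07; [1.960·√0.1302 + 0.842·√0.1284]² / 0.06² = 282.7, so 283.
- Post-MO(H): p̄ = 0.325; [1.960·√0.43875 + 0.842·√0.4275]² / 0.15² = 151.9, so 152.

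Both match the article.

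**2. Who is lost under the strict reading.** An event needs three consecutive months that satisfy the inequality. With counts 12, 10, 12 and nothing else near the limit, the patient is an event under ≥ and not under >. With 12, 10, 12, 12, 12 the patient is an event under both, because the last three months lie above 10.

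**3. Share of events lost (assumption-based).** The article gives no distribution of intake days. One model used 40,000 patients and 12 months of 28 days (336 days, matching the last visit in Table 1; the month length is an assumption). Monthly days were binomial, patient means logit-normal with between-patient SD 0.3 to 1.2, and extra month-to-month SD 0 or 0.4. The mean was set so that the inclusive rule gives the planned rate. The strict rule was then applied, for the 10-day and the 15-day limit separately.

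| Rate under ≥ | Events lost under > |
|---|---|
| 4% | 21–68% |
| 10% | 19–59% |
| 25% | 14–47% |
| 40% | 11–39% |

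A second model used rounded normal counts and the 10-day limit. With between-patient SD of 2–3 days, the 10% rate falls to about 4–6% and the 40% rate to about 23–29%. With SD of 4–6 days the loss is about 25–36% at the 10% rate and 15–23% at the 40% rate. In both models the loss is largest when patients are alike and cluster near the limit.

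**4. Effect on power if the loss L is proportionally equal in both arms.** Replace p₁ and p₂ by p₁(1−L) and p₂(1−L) and keep 283 and 152 per arm:

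z = [(p₁−p₂)·√n − 1.960·√(2p̄(1−p̄))] / √(p₁(1−p₁)+p₂(1−p₂)); power = Φ(z)

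Example, migraine, L = 10%: rates 9% and 3.6%; z = (0.054·√283 − 1.960·√0.118062) / √0.116604 = 0.69; power 75%.

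| L | Migraine | Post-MO(H) |
|---|---|---|
| 0% | 80% | 80% |
| 10% | 75% | 74% |
| 30% | 64% | 59% |
| 60% | 41% | 34% |

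Equal proportional loss is a simplification. In the first model, at the same spread (SD 0.5, no extra monthly variation, 10-day limit), a 10% rate loses 43% of events and a 4% rate loses 48%.

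**The case against.** The strongest reply is that the section answers the question itself. It ties the outcome to ICHD-3 and prints inclusive limits, and the thresholds in the next sentence refer back to them. What that sentence visibly changes is the duration, from more than three months to three or more. It gives no number for headache days, so it reads as shorthand. The article is a condensed text, and the app algorithm and analysis code are not shown. This much stands: the authors may well intend ≥, and events are lost only if the sentence is programmed literally. The contradiction remains. The sentence is worded as the trial's own rule and already departs from ICHD-3 on duration, so a reader could take the stricter inequality as a second deliberate departure. Trial design {8} also separates reaching a limit from passing it.

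The simulations are also open to a fair objection: they model the intake limit alone. The endpoint sentence also offers a headache-day route, and Inclusion criteria admit chronic migraine with at least 15 headache days a month. Some patients at the intake limit could qualify that way, so the loss is less certain than the ranges suggest.

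A reader might infer three stronger conclusions, and the article supports none of them.

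- *Some 30–60% of events would be lost.* That range depends on an assumed narrow spread between patients. Wider spreads give less.
- *Everyone with months at exactly 10 or 15 days is dropped.* A patient with another run of three months above the limit is still an event.
- *Events would be lost mainly in the intervention arm, creating or hiding an effect.* A warned patient who stops at the limit would end the month exactly on it, so the mechanism is conceivable. It requires alerts to fire at the endpoint limit, the article gives no alert number, and neither model contains alerts or two arms.

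**Conclusion.** The inconsistency is real, and it lies in the rule for the primary endpoint. The definition and the exclusion criterion count a month at the limit, and the alert wording also treats reaching its own, unnumbered limits as enough. The endpoint sentence, read literally, does not count such a month.

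The size cannot be taken from the article. Under the assumptions above, a literal reading loses roughly 11–68% of events on the intake limit alone. The power figures assume that the planning rates refer to the inclusive definition and that the loss is proportionally equal in both arms. On that basis even a 10% loss costs about five to six percentage points of power. A difference between the arms is possible if alerts share the endpoint limit, but its direction and size are not established. If the inclusive reading is what is programmed, no events are lost to the wording, and 283 and 152 per arm keep their 80% power.

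**What to change.** In Outcome assessment, replace *exceeded* with *reached or exceeded*, so that the endpoint sentence carries the definition's own ≥ for each limit. Use the same inequality in the app's endpoint algorithm and in the analysis code. Check both on test records at and just below each limit (9 and 10 days, 14 and 15 days), including a three-month run with one month exactly on the limit.

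The cost is a wording correction and one check of the endpoint code, with no new data and no extra patients. It is best settled before any outcome data are analysed.

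The headache-day alternative in the same sentence is a separate point. It has to be reconciled with the MOH definition, and changing the inequality does not settle it.
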